## Abstract

Physical activity and exercise are effective approaches in prevention and therapy of multiple diseases. Although the specific characteristics of lengthening contractions have the potential to be beneficial in many clinical conditions, eccentric training is not commonly used in clinical populations with metabolic, orthopaedic, or neurologic conditions. The purpose of this pilot study is to investigate the feasibility, functional benefits, and systemic responses of an eccentric exercise program focused on the trunk and lower extremities in people with low back pain (LBP) and multiple sclerosis (MS). A six-week eccentric training program with three weekly sessions is performed by people with LBP and MS. The program consists of ten exercises addressing strength of the trunk and lower extremities. The study follows a four-group design (N = 12 per group) in two study centers (Israel and Germany): three groups perform the eccentric training program: A) control group (healthy, asymptomatic); B) people with LBP; C) people with MS; group D (people with MS) receives standard care physiotherapy. Baseline measurements are conducted before first training, post-measurement takes place after the last session both comprise blood sampling, self-reported questionnaires, mobility, balance, and strength testing. The feasibility of the eccentric training program will be evaluated using quantitative and qualitative measures related to the study process, compliance and adherence, safety, and overall program assessment. For preliminary assessment of potential intervention effects, surrogate parameters related to mobility, postural control, muscle strength and systemic effects are assessed. The presented study will add knowledge regarding safety, feasibility, and initial effects of eccentric training in people with orthopaedic and neurological conditions. The simple exercises, that are easily modifiable in complexity and intensity, are likely beneficial to other populations. Thus, multiple applications and implementation pathways for the herein presented training program are conceivable.

**Trial registration:**
DRKS00020483 (DRKS, German Clinical Trials Register; 24^th^ January 2020 –retrospectively registered; https://www.drks.de/DRKS00020483).

## 1. Introduction

Physical activity and exercise are effective approaches in prevention and therapy of a range of diseases and clinical conditions [1]. Although there is a dose-response relationship between physical activity and premature mortality as well as primary and secondary prevention of chronic diseases [2], a defined recommendation for the type and dose of exercise needed in each case, as well as its delivery, remains to be clarified [1].

A combination of aerobic and strengthening exercises, as recommended by general international guidelines [3], seems to be vital to the promotion of health. Traditional strength training, containing concentric and isometric contraction exercises has been proven to be effective in the improvement of strength, function and overall quality of life as well as disease specific symptoms for a variety of clinical conditions [4–9]. Unfortunately, eccentric training, is not frequently applied in the therapy of clinical conditions, even though specific characteristics of lengthening contractions have the potential to be beneficial for many clinical populations [10].

As a muscle lengthens under tension during eccentric contractions, it is able to generate more force than during concentric or isometric contractions [11, 12]. It is assumed that due to the higher mechanical load applied, greater muscle hypertrophy can be achieved by an eccentric exercise training [12, 13]. In addition, eccentric muscle contractions lead to structural, physiological, and metabolic responses and adaptations. For example, eccentric loads result in a lower heart rate increase and lead to a reduced cardiovascular load compared with concentric contractions [14]. Moreover, the energy demand of eccentric contractions is up to four times lower than concentric muscle contractions at the same load [15–17]. Therefore, eccentric training seems particularly suitable for patient groups with metabolic, neurologic or cardiovascular diseases and impaired exercise capacity [18] as well as other chronic diseases associated with muscle atrophy, muscle weakness and reduced physical performance.

Regardless of the benefits, eccentric exercises may initially lead to muscle damage, impaired muscle function and delayed-onset muscle soreness, especially in unaccustomed loading situations. Therefore, it could be questioned whether the use of eccentric training in the therapy of clinical at-risk populations (e.g. elderly and frail people, people with diseases of the central nervous system, people with co-morbidities) is feasible [19]. Few studies have demonstrated that eccentric training is feasible and effective in cardiorespiratory disease [20], chronic obstructive pulmonary disease [21], after cancer therapy [22] and might also be relevant in obese patients [23]. Nevertheless, the transfer into the clinical practice is pending.

To date, the majority of eccentric training programs have been focused on orthopedic indications and prevention of muscular injuries [24, 25]. Considering eccentric muscle contractions result in decelerating movements that counteract gravity [26], eccentric training could also prepare the body, and especially the trunk, for high loads that may occur repeatedly and unexpectedly during daily and work-related activities. Therefore, it is potentially beneficial in the prevention and treatment of low back pain; one of the most common clinical conditions worldwide [27]. Generally, exercise can reduce the intensity of low back pain as well as pain-dependent limitation, improve function, and prevent recurrence [28, 29]. Although there is currently no evidence indicating a preferable mode, common recommendations emphasize that exercise programs should include elements to increase muscle strength and neuromuscular control, as these factors contribute significantly to maintaining trunk stability [30, 31]. Further, the ability of the neuromuscular system to adequately compensate for load-induced dysfunction and maintaining spinal stability is highly relevant in the prevention of low back pain and its patho-anatomical consequences. Surprisingly, despite its high potential to improve muscle strength and neuromuscular capacity, eccentric training has not been thoroughly investigated as a treatment of low back pain.

People with multiple sclerosis (MS) may also benefit from the aforementioned characteristics of eccentric exercises [18]. The MS disease process produces a diversity of neuropathological changes in the central nervous system, typically affecting a wide range of neurological functions including mobility, muscle strength, coordination, and sensation. Although there is a consensus that physical activity is imperative for people with MS, to date no specific exercise mode has been proven superior over others. In this case, eccentric exercises might be a valuable approach [32, 33]. Application of high loads to improve muscle force under reduced energy cost is essential for people with MS as their energy reserves are typically low and fatigue is elicited early [34]. Furthermore, increased stimulation of the cerebral cortex [35] and motor unit recruitment patterns, as well as cross-educational effects, may improve functional capacity [11]. Moreover, sensory and muscular impairments of the lower extremity are associated with an increased risk of falls in people with MS [36]. An eccentric training program addressing the lower extremity and the trunk potentially improving gait, balance and functional mobility might therefore be beneficial to reduce the risk of falling in this population.

Only few studies have evaluated eccentric exercises in people with MS. Recently, a small pilot study demonstrated the feasibility, safety and efficacy of eccentric downhill walking in five people with MS affected by ankle contractures [37]. Additionally, eccentric strength training of the elbow flexors was proven to be feasible as well as beneficial for strength- and function-related parameters in people with MS with spasticity [38]. Moreover, because of the possible anti-inflammatory effect of eccentric training, this exercise mode seems suitable for the modulation of the immunometabolism, since MS is associated with an altered balance between pro- and anti-inflammatory cytokines [39]. In this context, Berkowitz et al demonstrated that moderate aerobic exercises induced a similar acute cytokine response in women with mild MS as age matched healthy women, considering this exercise as safe and feasible [40]. Nevertheless, since eccentric strength training may induce muscle damage and is associated with an inflammatory response [41, 42], the influence of eccentric training on cytokine levels in people with MS still warrants clarification.

Although eccentric training has a high potential in the treatment of various clinical populations, more clinical trials focusing on feasibility and efficacy are required. Therefore, the aim of this multi-center pilot study is to evaluate the feasibility, functional benefits and cytokine response of an eccentric training program focusing on trunk, and lower extremities in individuals with low back pain and MS. The decision to focus on two different clinical populations, executing an identical exercise program, was implemented in order to expand the knowledge regarding this unique exercise approach.

## 2. Methods and materials

### 2.1. Overview of the study design

This assessor-blinded, bi-center, controlled pilot trial aims to evaluate the feasibility and benefits of a six-week eccentric training program with three weekly sessions (two center-based, one home-based), in individuals with low back pain (musculoskeletal condition) and people with MS (neurological condition). The focus is on the implementation of an eccentric training program directed to the trunk and major lower limb muscle groups. The overall approach includes a four-group bi-center design, in which three groups (A-C) perform an eccentric training program and one group receives standard care (D): (A) control group with healthy, asymptomatic people [CTRL]; B) people with low back pain [LBP]; C) people with MS [PwMS], D); people with MS who are receiving standard care physiotherapy [PwMS_STD_]. A test battery is applied to assess strength, function and patient reported outcome measures prior and following the intervention period. A schedule of enrolment, interventions and assessments is shown in **Fig 1** and the study design and flow in **Fig 2**. The study has been approved by the Ethics Committee of the University of Potsdam, Germany (ref. No. 44/2019) and the Institutional Review Board of the Sheba Medical Center, Tel-Hashomer, Israel (Nr. SMC-6288-19). Any kind of study amendment will be approved by the above-mentioned review boards prior to implementation and will be reported to the trial registry. The study is conducted and performed in agreement with the Declaration of Helsinki. This trial was registered under www.drks.de and the trial number is DRKS00020483 (DRKS, German Clinical Trials Register; 24^th^ January 2020). This paper is further prepared in accordance with the “Standard Protocol Items: Recommendations for Interventional Trials (SPIRIT)” guidelines (see **S1 Table**).

**Fig 1 pone.0270875.g001:**
[figure not shown]
Schedule of enrollment, interventions and assessments. EQ-5D: Questionnaire developed by the EuroQol Research Foundation to assess health status; TuG: Timed Up and Go test; 5-STS: Five-times Sit-to-Stand test; CPG: Chronic Pain Grade questionnaire; SF-36: Short Form 36 health survey; MSWS-12: 12-item Multiple Sclerosis Walking Scale; MFIS: Modified Fatigue Impact Scale; FES-I: Falls Efficacy Scale–International; NRS: numeric rating scale.

**Fig 2 pone.0270875.g002:**
[figure not shown]
Study flow and design, showing groups that are allocated to the intervention (dark grey) and the standard care (light grey). (A) LBP: participants with low back pain–intervention group; B) PwMS: people with multiple sclerosis–intervention group; C) CTRL: asymptomatic participants–intervention group; D) PwMS_STD_: people with multiple sclerosis–standard care; UP: University of Potsdam; TAU: Tel Aviv University).

### 2.2. Participants

The study is performed at two study centers, one in Germany and one in Israel. Participants of the CTRL and LBP group are recruited via the University Outpatient Clinic of the University of Potsdam, Germany. Participants with MS are recruited within the Multiple Sclerosis Center, Sheba Medical Center, Tel Hashomer, Israel. For the rational of a feasibility study a sample size of 12 participants per group is intended [43]. Participants (all sexes) aged between 18 and 65 years are included into this study. Participants eligible for CTRL group are healthy asymptomatic adults, with absence of any acute or chronic LBP. Asymptomatic participants with acute infections, pregnancy, or structural changes of the spine with or without neurological signs contra-indicating physical activities are excluded. Participants eligible for the LBP group need to report a minimum of 3 low back pain episodes within the last 12 month (not exclusively within the last 3 month) and report an average pain score of 3 or above on the numeric rating scale (NRS) within the last 3 months (NRS: numeric rating scale; 0: no pain; 10: worst imaginable pain). People with acute low back pain which occurred for the first time within the last 7 days, acute infections, pregnancy, or structural changes of the spine, with or without neurological signs contra-indicating physical activities are excluded. Participants eligible for PwMS and PwMS_STD_ group need a neurologist-confirmed diagnosis of definite MS according to the revised McDonald criteria, a score of <4.5 on the Expanded Disability Status Scale (EDSS), the ability to walk an equivalent of at least 500m without a walking aid and to be relapse-free for at least 90 days prior to testing. People with MS with cardiovascular disorders, respiratory diseases, the use of steroids or fampridine or other conditions contra-indicating physical activities are excluded.

### 2.3 Intervention programs

#### 2.3.1 Eccentric intervention

The program contains ten exercises addressing strength of the trunk and lower extremity, five exercises each for each body region (see **S1 Fig**). During execution of exercises, patients are instructed to emphasize the eccentric phase by performing the movement slowly and in a controlled manner against gravity. The program focuses on body weight exercises, complemented by resistance bands and small weights. Center-based training sessions are supervised by a team of experienced sport- and physiotherapists. Over the course of the intervention period (18 sessions total) each exercise is performed at least at six training sessions, ensuring a balanced and standardized exercise selection for all participants. Each training session comprises four to six individual exercises, which are performed for two to three sets with 10 to 15 repetitions each set. Intensity is controlled by a self-reported rating of perceived exertion (RPE) via the Borg Scale [44, 45]. Adequate training intensity is set by an RPE score between 13 and 17. Additional modifications regarding exercise complexity and intensity are made individually by controlling the range of motion, lever arms, motion velocity and use of additional resistance, respectively. For each training session RPE, pain intensity as well as muscle soreness are assessed (see **S2 Fig**). Overall weekly physical activity as well as all scores related to the eccentric program are documented and stored in a training log.

#### 2.3.2 Usual care for people with MS

The standardized physical therapy comprises twelve 40-45-minute individualized face to face physiotherapy sessions, over a 6-week period, plus an individualized 30-minute daily home exercise program. The standardized program of physiotherapy exercises aims at improving trunk and pelvic stability, lower limb muscle length, strength, balance and control of movement, in accordance with the Bobath concept [46]. This exercise program is reflective of the general exercises typically undertaken within routine clinical practice in people with MS.

#### 2.3.3 Adverse events

Adverse events like substantial increases in pain levels or any kind of symptom worsening are documented by either trained sport- and physiotherapist or the study team for events that occur during the intervention as well as during the baseline and follow-up assessments. If participants experience adverse side effects of the interventions or the test battery, consultation with a physician is sought to discuss necessary modifications or an early termination of the study.

### 2.4. Assessments/Procedure

#### 2.4.1 Experimental procedure

Potential participants learn of this study through personal contact, e-mails and printed advertisements posted at the two centers. The study team’s contact details are provided to enable interested participants to further enquire and participate in the study. Interested participants are provided with an information pack describing the study, supported by verbal information. They are screened for eligibility according to the pre-specified inclusion and exclusion criteria at the above-mentioned study sites. With inclusion criteria met, written informed consent of the participants are obtained. Group assignment is randomly performed where applicable by the principal investigators based on a generated list matched by age and gender. The randomization list is kept concealed (password protected, exclusively accessed by principal investigator) until intervention assignment. Only data analysts remain blinded to group allocation. Prior to the baseline measurement, participants undergo a physical examination (self-reported anamneses: verified diagnosis; current pain level, complaints and impairments; musculoskeletal/orthopedic examination) by a physician to rule out contraindications that restrict or prevent participation in regard to testing and exercise intervention. Baseline measurements (M1) are conducted three days before the first training session, comprising: (1) blood sampling, (2) self-reported questionnaires, (3) mobility, (4) balance and (5) strength testing. All participants, irrespective of group allocation, perform the test battery. Additional blood sampling is conducted immediately before and three days after the first training session in order to assess the acute reaction to the initial training bout. The follow-up measurement (M2) is conducted three days after the last training session. The follow up assessment session includes tests identical to those collected at baseline, with the addition of participant rating scores of the intervention program (5-point Likert-Scale regarding exercise selection, time effort and required equipment).

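### In the one comparison that can be randomised (PwMS versus PwMS_STD), allocation is not concealed from the role that assigns it, and as written assignment precedes the physician examination and M1

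*Protocol article*

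**What the plan says.** Section 2.4.1 of the protocol article (Experimental procedure) describes the steps in this order.

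- After screening against the eligibility criteria: "With inclusion criteria met, written informed consent of the participants are obtained".
- Then: "Group assignment is randomly performed where applicable by the principal investigators based on a generated list matched by age and gender".
- On custody of the list: "The randomization list is kept concealed (password protected, exclusively accessed by principal investigator) until intervention assignment".
- On blinding: "Only data analysts remain blinded to group allocation".
- Then: "Prior to the baseline measurement, participants undergo a physical examination", which is carried out "by a physician to rule out contraindications that restrict or prevent participation in regard to testing and exercise intervention".
- Then M1, of which it says: "All participants, irrespective of group allocation, perform the test battery".

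Section 2.1 introduces the study with the words "This assessor-blinded, bi-center, controlled pilot trial aims to evaluate the feasibility and benefits".

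Section 2.2 plans 12 participants per group. It recruits the asymptomatic and low back pain groups in Potsdam and both MS groups at the Sheba centre in Israel.

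**The concern.** Concealment protects a randomised comparison only if nobody who can influence entry knows the next assignment. Here the list is called concealed, yet the one role with access to it is the role that makes the assignment. If that role also has a say in who enters, or when, the next allocation could affect the decision.

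The order of steps adds a second route. The examination is a filter that can remove people. If it follows assignment, and only analysts are blinded from then on, nothing in the section keeps the examining physician from knowing the arm. The protocol's Introduction itself notes that eccentric loading can cause muscle damage, and that its use in at-risk groups, including diseases of the central nervous system, may be questioned. An examiner who knows the arm could therefore be stricter with the eccentric arm. People removed at that stage could be counted as drop-outs or as never enrolled, and the per-protocol comparison in Section 2.6 offers no check on this.

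The third route is M1. It includes maximal voluntary contractions and timed tasks, which depend on effort and can respond to knowledge of the arm in participant or tester.

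**Working it through.** The plan gives no figure to reproduce. This is mainly a comparison of statements, with one short illustration.

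**1. Which groups can be randomised.** Section 2.2 defines the asymptomatic and low back pain groups by health status and recruits them in Potsdam, so neither can be assigned at random. The two MS groups share one set of eligibility criteria and one recruiting centre. Random assignment where applicable can therefore only mean PwMS versus PwMS_STD: 2 × 12 = 24 people.

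**2. Who assigns and who has access.** Section 2.4.1 names the principal investigators as assigners and the principal investigator as the only person with access. The password keeps other staff out until assignment. It does not keep out the assigning role, and no separate list holder is named.

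**3. Where assignment falls in the sequence.** In text order: screening, consent, assignment, physician examination, M1. The sentence that everyone does the test battery whatever their allocation fits an allocation that already exists by M1, but does not prove it. No sentence dates the assignment, and Figs 1 and 2 (schedule and flow) are not available here.

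**4. Who is blinded afterwards.** Section 2.4.1 limits blinding to data analysts. Section 2.1 calls the trial assessor-blinded. Both can hold only if the assessors are the analysts, which is not stated. Which of the two describes practice at M1 cannot be settled from the text.

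**5. Illustration of size.** Planned arm size is n = 12 (Section 2.2). Two inputs are assumptions, not taken from the protocol: k participants are steered or removed, and each differs by d = 1 SD from those they replace or from the rest of the arm. Then

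shift of the arm mean = k × d / n

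- k = 1: 1 × 1 / 12 = 0.083 SD
- k = 2: 2 × 1 / 12 = 0.167 SD

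For scale, the standard error of a difference between two arms of 12, in SD units, is √(1/12 + 1/12) = √(2/12) = 0.41 SD. The two-person shift is about two fifths of that (0.167 / 0.41).

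**The case against.** The case on the other side has substance.

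- **Access.** A reader might infer that allocation is open to everyone running the trial. The text does not support that: recruiters, physicians, therapists and testers are shielded until assignment. The gap before assignment concerns one role.
- **Opportunity.** Foreknowledge biases selection only if its holder influences entry. The section does not say that a principal investigator screens, enrols or examines; screening is in the passive and the examination is by a physician. Assigners are plural and the access holder singular, and the centre where that person sits is not given. A holder in Potsdam cannot be ruled out.
- **Matching.** One might suspect that matching by age and gender lets candidates be steered into slots. The text does not say how matching works, so this is speculation.
- **Sequence.** The order is read from successive sentences. The examination is tied to M1, not to assignment, and the sentence on the test battery may simply mean that all four groups perform it.
- **Exclusions.** Contraindications to physical activity are already MS exclusion criteria in Section 2.2, and screening comes before consent. The examination may be a second check that removes few people, and both MS arms exercise.
- **Consequence.** The primary outcomes are feasibility measures, analysed descriptively. The MS contrast is preliminary and per protocol, so it already departs from the randomised comparison. The illustrated shift is well below the standard error.
- **Condensation.** An article may leave details of list custody to the full protocol.

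These points limit the finding to a possible bias of modest size. They do not remove it. The article does not merely omit custody: it states who assigns and who has access, and both are the same role. It also states that only analysts stay blinded, against its own design label. And although the contrast is secondary, Section 2.6 plans group-by-time tests on it, and Section 2.5.2 says the changes will inform later multi-center trials.

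**Conclusion.** The concern holds in a limited form. As stated, allocation in the MS comparison of about 24 people is not concealed from the assigning role. In the order written, assignment precedes both an examination that can still prevent participation and M1. The blinding statements in Sections 2.1 and 2.4.1 contradict each other and must be reconciled.

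Two stronger conclusions might be drawn, and neither is supported. The first is that selection was in fact biased: no sentence places the list holder in recruitment or examination. The second is that assessors are established to be unblinded: there are two conflicting statements, not a settled absence.

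The size, 0.08 or 0.17 SD on an arm mean for one or two participants, rests wholly on the assumed 1 SD difference and is an illustration, not an estimate. The sequence rests on sentence order. If assignment in fact follows clearance and M1, that part is resolved by a one-sentence clarification, but the question of who holds the list remains. This should be corrected; in a pilot with feasibility aims it does not invalidate the study.

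**What to change.** 1. Have the MS list held by someone who neither recruits nor assesses MS participants. Existing staff at the Potsdam centre qualify, since Potsdam recruits no MS participants.
2. Release each assignment only after consent, physician clearance and completed M1 are recorded for that participant, and state this order in Section 2.4.1.
3. Report any exclusions after assignment by arm, with reasons.
4. Reconcile the assessor-blinded label in Section 2.1 with the analyst-only blinding in Section 2.4.1, saying who is blinded at M1 and at M2.

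No new stratified or varying-block scheme is needed for this. With 24 people its value is debatable.

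**Cost.** One message between the centres per MS participant, with no added staff. First sessions can be booked only after M1, which is tight because M1 is placed three days before the first session. Section 2.1 requires both review boards to approve an amendment before it takes effect and requires it to be reported to the registry. Registration was retrospective, so some participants may already have been assigned. For them, the sponsor can still report who held the list, when assignment was made relative to clearance and M1, and the exclusions by arm.
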